**Data Analysis**

Impacts of the Simple and Comprehensive Interventions on EID testing rates, HIV-positive mothers and infants identified, and immunization data will be estimated by fitting multilevel linear probability and logit[[1]](https://inspir.bu.edu/Study_App.jsp?FORM_MODE=EDIT&tab=section&s=1371040947028" \l "_ftn1" \o ")  regressions that compare outcomes between program and comparison facilities while controlling for important covariates, such as historical EID and EPI rates, district, catchment population, facility staff, geography and patient characteristics. Data analysis will be conducted using Stata (version 12). The at-scale costs of both inventions will be modeled using external inputs as well as cost estimates from the evaluation intervention.  Moreover, operational best practices of this intervention will be assessed to determine the feasibility of scaling up either set of intervention nationwide.The primary analysis will be the logit regression.  These analyses relate to the primary study purpose as it will measure the change in EPI and EID uptake in a standard way while controlling for important covariates.  The qualitative focus groups will be used to examine the causal mechanisms of any impacts on outcome indicators but will not be used in the primary analysis.

**Technical study risks and potential biases**

The discussion below describes the approach towards potential research design effects that could pose threats to the integrity of the results of this evaluation.

Important steps will be taken to minimize the risk of Hawthorne effects, the process by which a subject of a study changes their behavior due to the knowledge that they are being surveyed and measured. For this evaluation, this is principally a problem for the EID and HIV testing outcomes of interest. Health facility staff may put extra effort into HIV testing in response to this project in addition to the intervention. To reduce this risk, the research team will work through Ministry of Health channels and District health officials as much as possible to more closely mimic typical managerial attention. This will better approximate Ministry oversight which will continue after the evaluation as compared to a pure research project. Analysis will also be done to see how consistent testing rates are across the duration of the experiment. The outcomes relevant to immunization uptake should not be affected by Hawthorne effects as they center on patient, rather than facility staff, behavior.

The study analysis will account for the risk of spillovers affecting the results of immunization uptake outcome variable between program and comparison facilities. Only one-third of facilities in the evaluation will be Comprehensive Intervention facilities which serve as the program group for the immunization uptake variable whereas the remaining two-thirds of the facilities will serve as a comparison group for this variable. There is a risk that, if the communication for the EID/EPI integration intervention is not properly targeted, mothers in comparison catchment areas may also receive the message. To minimize this risk, all messages will be highly associated to specific facilities via ANC, SMAGs, in-facility delivery, and PNC touch points, which are all facility-specific channels. However, the potential for word of mouth spread of information and communication spillovers remains. Therefore, the research team will analyze the immunization rates in the comparison sites against historical immunization data for these sites for significant changes over time. Finally, exit interviews will be conducted with comparison and program facility officials to check for observed changes in immunization attendance or rumors they may have heard from community members during the evaluation.

An additional spillover risk exists whereby mothers that ordinarily attend Comprehensive Intervention health facilities switch to other health facilities as a result of the Comprehensive Intervention. The study may collect immunization data from a subset of patients from health facilities neighboring Comprehensive Intervention facilities to estimate the magnitude of such potential shifts. Study sampling that maximizes the distance between study facilities will reduce the likelihood that comparison facility immunization rates are artificially increased due to new patients. Comprehensive Intervention facilities may still experience artificially low immunization rates due to transferring patients. Because estimating the proportion of patients that switch facilities that would remain at their typical catchment facility if the Comprehensive Intervention were universally implemented at every health facility would be extremely difficult, it is most appropriate to consider low immunization rates due to transferring patients as an impact of the Comprehensive Intervention although this could overestimate the effect the Comprehensive Intervention would have in a scaled-up environment.

There is a low risk of John Henry effect, the process in an evaluation by which the comparison group realizes that it is a comparison group and changes its behavior in response. Patients are unlikely to realize they are in comparison catchment areas and change their behavior in any way other than outlined in the spillover section. There exists a risk that comparison facilities could take steps to improve EID services that they would not have done in the absence of the evaluation. The research team will attempt to measure this by comparing EID testing rates from before the intervention with testing rates during the evaluation.

There is a low risk of any survey effects for this evaluation. No surveys with durations of over 30 minutes at a time are expected. Because the main outcomes are directly observed, not asked of the respondents, any survey effects are likely to be minimal.

*Site Attrition*

All sites included in the randomization will have appropriate infrastructure and staffing levels to participate in the study. Thus, it is unlikely that facilities will drop out from the study due to inability to implement the intervention. Because unexpected changes to staffing levels may still lead to attrition, additional facilities have been included in the sample size calculations to ensure adequate statistical power in the event of such occurrence.

*Patient attrition*

Patient-level attrition could manifest itself due to incorrect facility register recordings. This will be minimized through training and regular monitoring of facility health staff on proper register data collection. Respondent attrition is possible for those who do not consent to exit interviews. However, these activities are not central to the core analysis.

Bounds analysis will be used to account for any attrition in the ultimate analysis.

*Impact heterogeneity*

Facility registers provide important baseline data on HIV testing, EID, and EPI services and other patient characteristics. Additional baseline information on facility staff, equipment and buildings will be collected. This information will allow the study team to calculate whether the intervention had a differential impact across important variables.

Ethical Issues

We will seek approval from the ERES Converge Ethics Review Board in Lusaka, Zambia and the Boston University IRB. Study staff will comply with the relevant proposal submission policies of ERES Converge in order to gain full ethical approval to conduct the proposed study. After ethical clearance, the proposal will also be submitted to MoH for final permission to conduct the study.

*Risks to participants*

The proposed evaluation is likely to expose individuals to a minimal level of risk. This section will split risks considered into three sections: risks involving patient attendance, risks involving patient’s health facility experience, and risks involving the management of personal data.

Risks involving patient attendance to under-five health facilities are restricted to the Comprehensive Intervention evaluation group. This evaluation will be measuring whether fewer mothers will attend immunization services due to stigma issues surrounding HIV-testing or inconvenience caused by longer appointment times. This represents one of the primary outcomes measured in the study and thus will be monitored very closely. To minimize any potential adverse effects to uptake of routine immunizations, the Comprehensive Intervention will be discontinued if at any time after two months of data collection Comprehensive Intervention facilities are confirmed to have an immunization rate more than 20 percentage points lower than comparison and Simple Intervention Facilities.^[[34]](#footnote-12)^

For Comprehensive Intervention facilities, the patient experience for mothers will change as a result of the administration of the rapid HIV antibody test for mothers not already confirmed to be HIV-positive. This change in testing procedure will be communicated to mothers during the group counseling session so they are fully informed if they would like to opt-out from the HIV testing. Health facility staff will conduct standard counseling protocols if a mother does allow the rapid HIV antibody test to be conducted. The counseling protocol will be done in private, and contain information about the implications of the test and further options. In this way, mothers will be fully informed throughout of the HIV testing procedures and possibilities during the facility visit.

Risks involving data management and patient privacy apply to all study facilities. All test strips and dried blood samples will only be identified with an identification number, ensuring the privacy of all patients. All Ministry of Health HIV testing guidelines will be complied with, and all data will be collected by trained enumerators using paper surveys or electronic devices. Hard copy surveys will be kept in a locked storage room accessible only by study staff. All electronic data will be split into two separate files. Names and all other identifying information will be in one file and remaining data with unique individual identifications numbers will be in the second file. These files will be stored on two locked computers with password protected hard drives to ensure the confidentiality of the data. All data collected via electronic device by the enumerators will be transferred as soon as logistics permit to the research manager’s hard drive and subsequently erased from the enumerator’s digital device. Only 3DE staff conducting the study will have access to identifiable data. The Principal Investigator, [name], and Research manager, [name], will use STATA (version 12) to analyze the data. Primary data analysis will include quality control checks, such as checks for missing data and data entry checks. Data analysis will take place in Zambia.

*Potential benefits of the proposed evaluation*

The evaluation will directly benefit mother-infant pairs who are newly identified as HIV-positive or HIV-exposed during the study period and referred for treatment. If the interventions evaluated are found to be cost-effective, at-scale implementation will increase the number of mothers and infants identified as HIV-positive and the number of mothers and infants referred for treatment. This would be expected to have a positive impact on infant mortality and life expectancy. An increased identification of HIV-positive mothers and infant exposure risk will allow for more women to be put on lifesaving antiretroviral treatment and will contribute to the elimination of mother-to-child transmission of HIV. Selection of health facilities for the program and comparison groups will be done in an equitable, randomized manner. An additional likely outcome is that HIV-related stigmas could be reduced since HIV-positive mothers will no longer be specifically selected for extra activities.

*Informed Consent*

Informed consent will be sought from all study participants before any survey is implemented for study purposes. For any such activity, health facility and study staff will read aloud to participants the attached informed consent statement, which is in English and has been translated into the relevant local languages. The consent statement introduces the broad concept being studied, assures that confidentiality will be maintained, and makes clear that participants have a choice about whether to participate and that they may withdraw at any time. Informed consent will not be sought to copy routinely collected patient data recorded on health facility registers or for additional testing during under-five facility visits. In line with the 2008 Zambia Ministry of Health Guidelines on PMTCT, women who are offered opt-out HIV testing do not need to sign an informed consent form; they are only required to be fully informed of the test.^[[35]](#endnote-23)^

Discussion

Zambia’s Ministry of Health (MoH) leadership has expressed strong interest in increasing EID testing rates and in evaluating the integration of HIV services more closely with U5 services. As previously noted, several countries in Sub-Saharan Africa have formally or informally moved to integrate EID testing in under five health facility visits. Additionally, similar approaches have been the subject of research projects in Tanzania and South Africa; however, neither study was randomized to rigorously evaluate the effect on immunization rates or other important outcomes. This evaluation will fill a significant gap in knowledge in Zambia and in the broader literature on an important topic.

This randomized controlled trial will assess the impact of the Simple Intervention and Comprehensive Intervention on HIV testing rates, HIV-positive identification rates, and immunization uptake rates. The evaluation will provide MoH and MoCDMCH leadership with rigorous evidence to decide whether either set of interventions is worth scaling up and will provide additional policy-relevant insights in several related fields: 1) the feasibility of more closely integrating HIV services with other health services, 2) best practices and resources required to integrate HIV services with other health services and 3) the current efficacy of the PMTCT cascade in a high-prevalence rate of the country. The research questions and design of this study have been developed through consultation with key stakeholders in MoCDMCH, MoH, CHAI, IDinsight, and BU/ZCAHRD to ensure the highest level of rigor and policy relevance. All relevant partners will be informed of study results.

Limitations

It is unlikely that this study’s population will be perfectly statistically representative of the potential scale-up population. This evaluation focuses on rural, peri-urban, and urban areas of Choma, Livingstone, and Monze districts in the Southern Province of Zambia. Statistical power calculations have been conducted to determine effect sizes across the overall sample. Therefore, the research team may only be able to draw indicative results on differences in some of the outcomes variables in urban areas as compared to rural areas. The study will be conducted in medium to high HIV prevalence areas that may differ from low prevalence areas.

The study will only test one approach to reinforcing testing guidelines and one approach to integrating services more closely. It is possible that other approaches to these broad objectives could have different impacts on the outcome variables of interest.

This study may estimate spillover effects due to patients transferring from Comprehensive Intervention to comparison facilities but will not attempt to estimate the proportion of transferred patients that would have remained at their original facility if the Comprehensive Intervention were universally implemented in all facilities. As a result, impacts on immunization rates are likely to be overestimated, and impacts on HIV-related indicators likely to be underestimated. Both of these biases are in the conservative direction. This is deemed acceptable given the policy-focus of this evaluation and that any study conclusions should account for the worst possible policy scenario – which the approach to spillovers should enable.

Finally, due to logistical considerations, the study does not attempt to integrate EID services with outreach EPI services, where health staff members travel to communities to administer routine under-five immunizations. Likewise, this will shade the impacts on immunization rates and HIV-related indicators conservatively, which is ideal to draw policy implications from the study.

Dissemination of Findings

The outcomes and analysis, along with a final recommendation, will be compiled into a study report and policy brief for the MoH and MoCDMCH. If this intervention is scaled up across the country, CHAI and IDinsight will continue to work with the partners to monitor the project’s status. Any findings from this longer-term monitoring period will be added to the policy brief. Contingent on MoH and MoCDMCH approval, findings will be shared with the Zambian and global health community to learn how EID testing rates can be increased and how HIV services can be better integrated with immunization services.

Budget

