- Operational integration of Early Infant Diagnosis (EID) and Expanded Program of Immunization (EPI)
- Training and orientation of health facility staff to deliver intervention messages to mothers of children under five years

1. Control: Usual standard of care.

We will then evaluate the two interventions in comparison to the control group, as well compare the two intervention groups to each other, in terms of specific outcomes (See the power calculations section for specific outcome variables) by a review of clinic records collected over the period of the study.

We will supplement and triangulate the data obtained from the clinic records through four primary data collection tools:

- Focus Group #1: Mothers who have recently attended Under-5 clinics
- Focus Group #2: Health facility workers in sampled health facilities Interview guide for exit interviews for mothers done at health facilities
- Interview guide for data verification for mothers done in local communities

Random sampling will be done at the health facility level to separate health facilities in the sample frame into 4 groups – 1) Comparison 2) Simple Intervention 3) Comprehensive Intervention and 4) Not in the study sample. Sampling will be conducted using STATA IC Version 12 with a pre-set seeds to allow for post-randomization verification of selection methods. There are 77 clinics in the sample frame spread across three districts in Southern Province in Zambia. The sample will be stratified by urban/rural divide and by district. Please see the table below for information on the stratification within the sample frame and sample respectively.

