**Table 1: Sample Stratification**

|  | Total Facilities | Total Urban | Total Rural | Sample Total | Sample Urban | Sample Rural |
| --- | --- | --- | --- | --- | --- | --- |
| Choma | 37 | 6 | 31 | 30 | 6 | 24 |
| Livingstone | 15 | 11 | 4 | 9 | 9 | 0 |
| Monze | 25 | 3 | 22 | 21 | 3 | 18 |
| Total | 77 | 20 | 57 | 60 | 18 | 42 |

Sampling of clinics will not be weighted by population; therefore, individuals who live in facilities with smaller catchment areas have slightly higher probability of being included in the study than those that live in the catchment area of larger facilities. Within each strata, each facility has an equal chance of being allocated into each of the three evaluation arms. Randomization will not occur on site but will be conducted before the interventions begin. Please note, at the time of submission to IRB, the final sample has not been run in STATA.

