2) Changes to Testing Algorithm – The research team will conduct a short training on changes to the HIV testing Algorithm that has been approved by Zambia’s Ministry of Health for this evaluation. This training will be a part of the clinic flow optimization workshop mentioned above. Currently, only mothers who have not been tested in the last 3 months are supposed to be tested at under-5 clinics, although adherence to this guideline is poor. Under the study design, all mother-infant pairs will be tested for HIV at their first under-5 visit (at 6 weeks) unless they have previously tested HIV-positive.

Evaluation Activities:

We shall randomly select 60 health facilities from a total of 77 in Southern province of Zambia (see sample size section). These health facilities will be randomly allocated into three study arms. All facilities will receive basic training on proper patient documentation across the different registers used to record EID, EPI, and under-five year old children visit information.

*1.0 Review of health facility client records, supplemented by review laboratory data for verification*

A field team of no more than 6 field officers will visit the 60 health facilities once every 2 weeks. Administrative data, meaning aggregated patient data, will be collected from health facility tally sheets and registers and inputted in aggregate form into mobile phones using google.org’s Open Data Kit application. Different data points will be drawn from different registers:

- Immunization data will be collected from all health facility tally sheets
- HIV Rapid Test Data will be collected from Tally Sheets and the BU Integrated PMTCT Register
- HIV Dried Blood Spot (DBS) testing data will be collected from the DBS tracking register and confirmed by data in laboratory data base at the University Teaching Hospital in Lusaka.

*2.0 Focus Group Discussions (FGDs) with mothers who have recently attended Under-5 clinics*

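### The protocol relies on sampling that spaces study facilities apart, but the sampling it describes has no distance rule to keep transferred mothers from raising comparison-site immunization rates

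*Protocol*

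**What the plan says.** **The safeguard.** In Technical study risks and potential biases, the protocol considers mothers who leave Comprehensive clinics for other facilities and states: "Study sampling that maximizes the distance between study facilities will reduce the likelihood that comparison facility immunization rates are artificially increased". The same section, and later Limitations, accept that Comprehensive rates may look low because of transfers. They treat this as part of the intervention's impact and call the resulting bias conservative.

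**The sampling.**
- Study Design and Procedures, Design: "Random sampling will be done at the health facility level to separate health facilities in the sample frame into 4 groups" (the three arms and a group outside the study), and "The sample will be stratified by urban/rural divide and by district".
- Evaluation Activities: "We shall randomly select 60 health facilities from a total of 77 in Southern province of Zambia".
- Text below Table 1: "Within each strata, each facility has an equal chance of being allocated into each of the three evaluation arms". The same paragraph says the final sample had not yet been run.
- The totals row of Table 1 reads "Total | 77 | 20 | 57 | 60 | 18 | 42" (all, urban and rural facilities in the frame, then the same three for the sample).

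Sample Size and Justification repeats the stratified random selection. Geographic dispersion appears only there, as one reason for choosing the three districts.

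**The before/after checks.** For communication spillover, comparison-site immunization rates are set against the same sites' historical data. For John Henry effects, the check consists of "comparing EID testing rates from before the intervention with testing rates during the evaluation". Evaluation Activities also says: "All facilities will receive basic training on proper patient documentation across the different registers". The registers concerned record EID, EPI and under-five visits.

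**The concern.** The immunization outcome is a primary outcome, and its denominator for each facility is the number of women attending antenatal care (footnote to the immunization outcomes in Study Aims). A mother who attends antenatal care at a Comprehensive clinic and then has her infant vaccinated elsewhere stays in the first clinic's denominator, while the dose enters another clinic's numerator. If that clinic is a Simple or Comparison site, one transfer lowers one side of the contrast and raises the other. A fall in immunization could then be reported although no infant missed a vaccine. The discontinuation rule in Ethical Issues uses the same contrast and would carry the same bias.

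The protocol offers spaced sampling as its protection against the rise on the comparator side. If the sampling does not space facilities, that protection is missing. The historical checks are a weaker backstop if recording practice changes between the two periods being compared.

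**Working it through.** **1. Table 1 reproduced.** The district rows sum to 77 facilities (20 urban, 57 rural) and a sample of 60 (18 urban, 42 rural), as printed.

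**2. Room for a spacing rule.** With N facilities in a stratum, n sampled and c = n/3 per arm, a randomly chosen other facility in a Comprehensive site's stratum is a Simple or Comparison study site with probability 2c/(N − 1).

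| Stratum | n of N | Sampled | c | 2c/(N − 1) |
|---|---|---|---|---|
| Choma urban | 6 of 6 | 100% | 2 | 4/5 = 80% |
| Monze urban | 3 of 3 | 100% | 1 | 2/2 = 100% |
| Livingstone urban | 9 of 11 | 81.8% | 3 | 6/10 = 60% |
| Choma rural | 24 of 31 | 77.4% | 8 | 16/30 = 53% |
| Monze rural | 18 of 22 | 81.8% | 6 | 12/21 = 57% |

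None of the 4 rural Livingstone facilities is sampled. Overall 60/77 = 77.9% are taken, and 18/20 = 90% of urban ones. In the Choma and Monze urban strata only one sample is possible, so the spacing of sites cannot be chosen. In the other sampled strata a rule is possible, but none is stated.

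**3. Size of the effect.** Inputs from the power section are 20 Comprehensive against 40 other facilities, 87% expected DPT1 uptake and a 10-point detectable decrease. Assumptions are equal-sized facilities, no infant truly lost to vaccination, and a share s of vaccinated infants of Comprehensive mothers taken outside the Comprehensive arm after antenatal care. The protocol gives no value for s. Moves between two Comprehensive sites cancel in the arm mean and are not counted in s.

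- Fall in the Comprehensive rate: 87 × s.
- Rise in the comparator rate if every switcher goes there: 87 × s × 20/40 = 43.5 × s. If all leave the study sites: 0.
- Apparent difference: from 87 × s to 1.5 × 87 × s.

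| s (assumed) | Apparent fall, points | Of which comparator inflation |
|---|---|---|
| 2% | 1.7 to 2.6 | 0 to 0.9 |
| 5% | 4.4 to 6.5 | 0 to 2.2 |
| 10% | 8.7 to 13.1 | 0 to 4.4 |

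Switching alone gives an apparent 10-point fall at s = 10/(1.5 × 87) = 7.7% if all switchers reach comparators, or s = 10/87 = 11.5% if all leave the study sites.

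**4. The historical checks.** Immunization counts come from facility tally sheets. All facilities, comparison sites included, are trained in documenting EID and EPI. If recording improves as intended, a before/after change at a comparison site mixes recording with any spillover or extra effort. The document gives neither the size nor the direction of the effect. Because every arm is trained, the effect is in principle common to all arms.

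**The case against.** The strongest reply is that the protocol has already dealt with transfers. It says low Comprehensive rates caused by them will count as impact, and Limitations mentions movement to comparison facilities and says the immunization effect is likely overestimated, in a conservative direction. This stands for the fall within Comprehensive sites, which is the larger part of the figures above. It does not settle the comparator side: the direction is admitted, but the only limit offered on size is a sampling rule that the design does not contain. Data from facilities neighbouring Comprehensive sites could measure switching, but collecting them is optional.

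A reader might also infer more than the documents support:

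- *That every spillover safeguard fails.* Facility-specific messaging and exit interviews with facility officials are not contradicted. The historical immunization check was written for communication spillover and the EID check for John Henry effects; neither was meant to detect transfers.
- *That a mother leaving a Comprehensive clinic must end up in a comparator.* Hospitals and inadequately staffed facilities lie outside the frame, about a quarter of immunizations are done on outreach, and another Comprehensive site may be nearby. The 1.5 multiplier is therefore a ceiling. The two strata taken whole contain only 3 of the 20 Comprehensive sites (2 in Choma, 1 in Monze).
- *That documentation training biases the trial result.* It reaches all arms, so it does not by itself bias the between-arm comparison. DBS data are also confirmed against the laboratory database, and under-5 cards are compared with registers during the study.

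**Conclusion.** The point holds as a contradiction within the protocol. A stated protection for a primary outcome has no counterpart in the sampling procedure, cannot be met by choice of sites in two strata, and is not specified in the rest.

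The part left unprotected is comparator inflation of at most 0.5 × 87 × s: up to 2.2 points at 5% switching and 4.4 at 10%. The full apparent fall is 4.4 to 6.5 and 8.7 to 13.1 points respectively, but most of it is an effect the protocol openly accepts. These figures rest on an assumed s, equal facility sizes, 87% uptake and switching after antenatal care. They show what is possible and do not predict what will happen.

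Confounding of the before/after checks by the documentation training is a sound inference of unknown size, and it concerns those checks only. The changes should be made before the sample is drawn, but the randomized design is not undermined.

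**What to change.** 1. Delete the distance sentence or make it true where the strata allow. The sample is not yet drawn, so the draw and the allocation can be restricted to keep Comprehensive sites apart from comparators, with the rule stated. In Choma and Monze urban only the allocation is open; in Monze urban, with one site per arm, both other sites are comparators whatever is done. The restriction should preserve each facility's equal chance of each arm, or the text below Table 1 must change.
2. Pre-specify a sensitivity analysis of Comprehensive sites against comparators that do not neighbour one. This needs facility locations and a definition of neighbouring fixed in advance. The cost is lower precision.
3. For the historical checks, compare changes over time between comparison sites near to and far from Comprehensive sites, so that a training effect common to both cancels.
4. Base the before/after EID check on laboratory counts, allowing for samples rerouted to newly opened laboratories. Background and Introduction mentions one planned in Livingstone, a study district.

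Total DPT1 doses per stratum against the previous year would not serve as a bound. They rest on the same facility records, so the training may affect them, and they change when mothers move outside the study sites or to another stratum.

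The cost is protocol wording, a restricted draw, facility locations and some added analyses, with no extra participants.
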